**Laboratory samples (only Lausanne)**							
Blood (50ml/sample)	X	X				X	
Urine (5 to 300 ml/sample)	X	X				X	
Stools	X	X				X	
Arginine level	X	X					
Tissue (ASS1 expression analysis)		X					
Fresh Tissue (oncological patients)		X					
Influenza vaccination	X						
NRS	X						
Eligibility and Randomization	X						
Post-operative infectious complications						X	X
Comprehensive Complication Index (CCI)						X	X
EORTC-QLQ-C30 questionnaire	X					X	X
Peri-operative management					X		

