### Choice of comparators and protocol adherence

Oral Impact^®^ (IN) is an immune-modulating nutritional supplement containing arginine, omega-3 polyunsaturated fatty acids, and ribonucleic acid. Arginine is a key amino acid involved in multiple cellular processes as well as in lymphocyte function and its deficiency results in impaired adaptive immune response. It plays an active role in wound healing, muscle repair (by protein translation), and thrombosis prevention. The present design raises the issue of supplementing patients that are not at nutritional risk with Oral Impact®, resulting in overnutrition with potentially deleterious clinical consequences. However, this hypothesis has not been confirmed by others [23] and the product’s brochure stipulates that the administration of Oral Impact® in the preoperative phase is also indicated in well-nourished patients [24]. Moreover, surgery induces arginine deficiency and many patients with normal preoperative arginine concentrations cannot endogenously satisfy the metabolic demand after surgery.

Patients will be randomly assigned to receive 7 days of preoperative IN, three times a day (Oral Impact^®^) or will not receive oral IN supplements. Carbohydrate loading and protein drinks will be allowed in both groups. In the interventional group, patient’s compliance to the allocated treatment will be recorded by asking the patient how many nutritional supplements she/he has ingested preoperatively (ranging from 0 to 21 bags). Compliant patients will be defined by having drunk at least 14 of the 21 allocated nutritional supplements. To objectively verify and validate these subjective data, serum arginine levels will be assessed at enrolment (between day − 30 and day − 8) and at preoperative admission after intake of the allocated nutrition (day − 1).

Potential effective crossover between intervention groups will be assessed and recorded. As usual with interventions requiring voluntary adherence to a protocol, there is a risk for some participants from the IN arm do not comply with the intervention. Moreover, a mirroring risk exists for participants from the control group to access IN independently of the study protocol, since the product is commercially available. Recording such protocol deviations is mandatory for processing to a second line per-protocol analysis. However, the risks of crossover are very low.

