### Statistical analysis

Ordinal and continuous data will be presented by study group in the form of descriptive statistics, as number of patients, mean, standard deviation, minimum, median, and maximum. Categorical data will be presented by study group using contingency tables with absolute and relative frequencies.

Complications rate will be presented using contingency tables with absolute and relative frequencies, overall and then by study group. The complication rate will be compared between groups using a Chi2 test. Mortality after surgery and postoperative complication-free survival will be analyzed using Kaplan–Meier curves. The study groups will be compared with a log-rank test. Nutritional status will be documented, and subgroup analysis of well-nourished patients randomized to the IN group will be undertaken at the end of the study. No imputations will be done on missing data. So, for longitudinal analysis mixed method analysis will be performed. Non-compliant patients from both arms will be maintained in the study, with no exclusion from the primary intention-to-treat analysis, however withdrawn from the per-protocol analysis. There is no data monitoring committee, owing to very good and well-known safety profiles of the IN and to the short follow-up period.

Other subgroup analyses will be performed (1) to test the effect of neoadjuvant chemotherapy and the risk of malnutrition on the primary outcomes and (2) to test the impact of the ERAS® compliance on the primary and secondary outcomes.

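### The second-line per-protocol analysis can remove non-takers from the immunonutrition arm only, so it is open to selection bias, plausibly but not certainly in favour of immunonutrition

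*Protocol article*

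**What the plan says.** The protocol article, Statistical analysis, states the rule for both analysis sets in one sentence: "Non-compliant patients from both arms will be maintained in the study, with no exclusion from the primary intention-to-treat analysis, however withdrawn from the per-protocol analysis". The words that matter for this point are the last ones, "however withdrawn from the per-protocol analysis".

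Compliance is defined under Choice of comparators and protocol adherence: "Compliant patients will be defined by having drunk at least 14 of the 21 allocated nutritional supplements". It is recorded in one arm, by self-report: "In the interventional group, patient’s compliance to the allocated treatment will be recorded by asking the patient how many nutritional supplements she/he has ingested preoperatively". For controls the same section describes a single deviation, obtaining the product outside the trial: "a mirroring risk exists for participants from the control group to access IN independently of the study protocol, since the product is commercially available". It then adds: "However, the risks of crossover are very low". The section calls the per-protocol analysis second line; intention-to-treat is primary.

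On verification, the section says: "To objectively verify and validate these subjective data, serum arginine levels will be assessed at enrolment", with a second measurement at preoperative admission. That sentence names no site. In Table 2 the arginine row stands under a heading that begins "Laboratory samples (only Lausanne".

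**The concern.** The wording on both arms suggests a symmetric exclusion, but the two arms are filtered on different behaviours. An IN patient leaves the per-protocol set for taking too little of a product that was offered. A control patient leaves it only for obtaining a product that was not offered. A control who would have stopped drinking the supplement after three days looks like any other control and stays in.

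The comparison is therefore between IN patients selected by their own behaviour after randomisation and a nearly unselected control group. If those who fall below 14 bags differ in infection risk from those who reach it, the two groups differ even when IN does nothing. At stake is the reading of the per-protocol result: a gap between it and the intention-to-treat result could be taken as the benefit of actually drinking the product when part or all of it is selection.

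**Working it through.** **The plan's own figure.** Sample size calculations gives 37% against 20%, two-sided 5% and 80% power. With pooled variance and no continuity correction, n per arm = [1.96·√(2·0.285·0.715) + 0.842·√(0.37·0.63 + 0.20·0.80)]² / 0.17² = 109.5, so 110. Then 220/0.95 = 231.6, so 232. Both stated figures reproduce. They concern the primary analysis and are not touched by this point. The article states no figure for the per-protocol analysis.

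**Size of the possible bias.** Inputs from the document: 37% infections, 110 informative patients per arm. Assumed inputs, which the document does not give: the share q of IN patients below 14 bags, and the ratio R of their infection risk to that of compliers. Assume no IN effect, so the whole IN arm has 37%, and no control is excluded. The complier risk p solves (1−q)·p + q·R·p = 0.37, so

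p = 0.37 / [(1−q) + q·R], and the spurious difference in favour of IN is 0.37 − p.

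| q | R | p | Difference favouring IN (points) |
|---|---|---|---|
| 5% | 1.5 | 0.37/1.025 = 36.1% | 0.9 |
| 5% | 2.0 | 0.37/1.05 = 35.2% | 1.8 |
| 20% | 0.67 | 0.37/0.934 = 39.6% | −2.6 |
| 20% | 1.0 | 0.37/1 = 37.0% | 0.0 |
| 20% | 1.5 | 0.37/1.1 = 33.6% | 3.4 |
| 20% | 2.0 | 0.37/1.2 = 30.8% | 6.2 |
| 30% | 2.0 | 0.37/1.3 = 28.5% | 8.5 |

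The last row is half the planned 17 points, but it takes the most extreme pair of assumptions.

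**False significance.** Take q = 20%, so 110 controls and 110·0.8 = 88 IN patients. The normal-approximation chance of a significant result favouring IN is 1.0%, 2.5%, 7.0% and 14.5% at R = 0.67, 1.0, 1.5 and 2.0. The nominal value is 2.5%.

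**Over-reported intake.** Take q = 20% and R = 1.5, and let a share m of non-compliers claim at least 14 bags. They stay in the IN set, whose rate becomes [0.8·0.336 + 0.2·m·0.505] / (0.8 + 0.2·m). The spurious difference is 3.4, 2.4, 1.5 and 0.0 points at m = 0, 25%, 50% and 100%. Misreporting moves the result back towards intention-to-treat.

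**The randomisation-based alternative.** The complier average causal effect is the intention-to-treat difference divided by the difference between arms in the share who took the product. With no effect and q = 20% it is 0/0.80 = 0, whatever R is. Treating uptake as known, its interval is 1/0.80 = 1.25 times as wide as the intention-to-treat interval. The naive per-protocol interval is about √[(1/110 + 1/88)/(2/110)] = √1.125 = 1.06 times as wide.

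**Arginine coverage.** Planned recruitment is 50, 25 and 10 per year, so Lausanne supplies 50/85 = 59%. The other 35/85 = 41% would have self-report only.

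**The case against.** The strongest reply is that the plan already ranks its analyses properly. Intention-to-treat is primary and excludes nobody, per-protocol is second line, crossover is to be recorded, and nowhere is an efficacy claim tied to the per-protocol result. The weakness is also shared by any per-protocol set with an untreated control arm, and a condensed article may leave adjustment and labelling to the full protocol. All of this limits the weight of the point. It does not remove it, because the objection is to the exclusion rule that the article does state, not to a missing adjustment.

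Three stronger readings are tempting, and the documents do not support them.

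- A reader might infer that the analysis is certain to favour IN. The Introduction calls malnutrition an independent risk factor for morbidity, and the section on discontinuing interventions names severe diarrhoea or nausea as possible side effects. That makes higher risk among non-compliers plausible. Nothing states it, and the table shows the bias vanishing at equal risk and reversing below it.
- A reader might infer that Lausanne-only verification adds to a bias towards IN. Over-reporting works the other way, and the article does not say that arginine defines the per-protocol set.
- A reader might infer that no control can be excluded. Controls who obtain IN are removed; it is the counterparts of IN non-takers who cannot be.

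The Table 2 reading is probable rather than certain, since the end of the Lausanne-only block is not visible in the extracted text. Arginine does sit among the sample rows, and the Abstract and Exploratory outcomes both confine sampling to Lausanne.

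The alternative estimator has its own weak spot: with 14 bags as the cut-off, it assumes that smaller amounts do nothing.

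**Conclusion.** The point holds as a weakness of a secondary analysis. As written, the per-protocol rule compares self-selected IN takers with an essentially unselected control arm, so its result does not carry the protection of randomisation. The sign of the bias is unknown but plausibly favours IN. Across the assumed 5% to 20% of non-compliers with 1.5 to 2.0 times the risk, it amounts to 0.9 to 6.2 points against a planned effect of 17. These sizes rest on assumed non-complier shares and risk ratios; only the 37%, the 17 points and the 110 per arm come from the protocol. The primary analysis and the sample size stand.

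The arginine question is separate: the text and Table 2 disagree on coverage. That limits how far reported intake can be checked; it is not a cause of bias towards IN.

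**What to change.** 1. Estimate the effect in compliers as a complier average causal effect, with randomisation as the instrument and intake of at least 14 bags as treatment received. IN-arm bag counts are already collected. Crossover in controls is already to be recorded, and the number of bags should be noted for them too.
2. Repeat it with any intake as treatment received. If partial intake has an effect, the 14-bag version credits that effect to the full compliers; the any-intake version avoids this.
3. If the naive per-protocol comparison is kept, label it descriptive and draw no efficacy conclusion from it.
4. Reconcile the arginine sentence under Choice of comparators and protocol adherence with Table 2. If Lausanne only is meant, say that the objective check covers about 59% of planned patients.

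The cost is a little more analysis, a wider interval than the naive comparison gives, and reliance on the exclusion restriction, which should be stated. The estimate still depends on self-reported bags: over-reporting enlarges the denominator and pulls it towards the intention-to-treat difference. No new trial procedure is needed.

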### Insurance

In the event of study-related damage or injuries, the liability of CHUV, as the sponsor, provides compensation, except for claims that arise from misconduct or gross negligence.

### Publications

The results of the projects will be published in peer-reviewed open access scientific journals, in the Clinical Trials register, and presented in scientific congresses. Authorship to publications will be granted according to the rules of the International Committee of Medical Journal Editors (ICMJE). In addition, data of each resulting article with be published on an open data repository (Zenodo). The datasets analyzed during the current study and statistical code are available from the corresponding author on reasonable request, as is the full protocol.

## Conclusion

There is an urgent need of improvement in the perioperative management of cystectomy patients. The INCyst Trial will challenge the added value of preoperative IN in patients undergoing cystectomy, possibly reducing the postoperative morbidity and mortality. It might bring breakthrough changes in the daily urology clinical practice that would also be relevant in other medical disciplines practicing heavy surgeries. Plus, it will provide invaluable data on the host immune response and microbiota composition.

## Data Availability

Datasets generated during the study will be kept by the corresponding author and made available upon request.
